## Abstract

Fibromyalgia (FM) is a complex disease that is characterized by chronic musculoskeletal pain and has great economic impact. FM prevalence is about 2% to 4% worldwide, affecting mainly middle-aged women, and its complex pathophysiology complicates diagnosis, treatment and the findings of solid biomarkers. Previous studies have suggested an association between the disease and oxidative stress, mitochondrial metabolism, intestinal microbiota and inflammation, providing sufficient data to support the multifactorial origin of FM. Hence, the objective of this randomized, prospective, low-interventional, double-blinded and placebo-controlled clinical trial is the development of a specific panel of FM biomarkers and the evaluation of their response to a six-month nutritional intervention based on the Mediterranean diet supplemented with extra virgin olive oil (EVOO). For this purpose, the experimental design implies the recruitment of a large cohort of female Spanish patients. Middle-aged women who meet the diagnostic criteria for FM according to the American College of Rheumatology (ACR) will be eligible, along with age-matched healthy women. Both groups will be randomly divided into placebo (olive oil, OO) and treatment groups (extra virgin olive oil, EVOO), and will provide samples at the beginning (T_0_), after 3 months of nutritional intervention (T_1_), at the end of the nutritional intervention in 6 months (T_2_), and 6 months after the end of nutritional intervention (T_F_), being enrolled for 1 year. Data will be collected through health questionnaires, and whole blood and stool samples will be taken and analyzed. Blood will be used for western-blotting and proteomic analysis of mitochondrial homeostasis and plasma proteome, while stool will undergo metagenomic analysis, respectively. This study represents the first low-interventional investigation with more than 200 participants focused on exploring the association of oxidative stress, mitochondrial metabolism, intestinal microbiota and related pathways with a nutritional intervention in the context of FM. As a result, the outcomes of this study will significantly contribute to the development of a comprehensive and robust panel of diagnostic biomarkers, and will shed some light on their modulation with non-pharmacological therapies such as nutrition.

**Clinical trial registration**: https://clinicaltrials.gov/study/NCT05921409, identifier: NCT05921409.

Traditionally, FM has been associated with oxidative stress and mitochondrial dysfunction. Oxidative stress is defined as an imbalance between reactive oxygen species (ROS) and antioxidant levels in the body. The production of ROS appears to be primarily attributed to the mitochondria, which are unique energy-producing organelles in cells and have their own genome. Excess ROS or compromised mitochondrial antioxidant defense result in detrimental effects on essential biomolecules such as DNA, proteins, and lipids (5). This impairment can result in compromised mitochondrial function (6). Moreover, it triggers the liberation of pro-apoptotic proteins from the mitochondrial intermembrane space, initiating the process of cell death activation, which is known as mitophagy (7). This process governs the removal of damaged mitochondria, whereas the opposite process, called mitochondrial biogenesis, generates new functional organelles (7). Some authors have conducted studies to investigate variance in mitochondrial mass protein levels among chronic fatigue syndrome (CFS) and FM patients (8). The studies have revealed that FM patients exhibit lower levels of the peroxisome proliferator-activated receptor-gamma coactivator 1 alpha (PGC-1α) and the mitochondrial transcription factor A (TFAM), whereas CFS patients did not display significant changes in these proteins. TFAM plays a crucial role in human mitochondrial DNA transcription and works as a key regulator of mitochondrial DNA copy numbers. These discrepancies in mitochondrial protein levels between the two conditions offer valuable insights into their respective pathogenesis. Moreover, they hold the potential to facilitate the development of novel biomarkers that can effectively differentiate between CFS and FM. Recent research has demonstrated a reduction in the activity of antioxidant enzymes such as superoxide dismutase 1 (SOD1), catalase (CAT) and nicotinamide adenine dinucleotide phosphate (NADPH), which correlates with the severity of pain and fatigue in FM patients (9). Furthermore, Altindag and Celik (10) observed lower total antioxidant capacity (TAC) among individuals with FM, and multiple studies have shown in FM patients decreased levels of CoQ10, a relevant enzyme for mitochondrial function (7). Additionally, mitochondrial imbalance in FM manifests itself as an increased expression of autophagic genes and the elimination of damaged mitochondria (7). Mitochondria-derived ROS play a key role in stimulating the activation of mediator signaling molecules, including the nuclear transcription factor kappa-B (NF-κβ). Consequently, this activation leads to an up-regulation of inflammatory cytokines, such as interleukin-1β (IL-1β) and tumor necrosis factor-α (TNF-α), and FM has consistently been linked to a low-grade inflammation profile. Notably, NF-κβ is activated by a critical type of membrane receptor associated with oxidative stress and inflammation. The regulation of this receptor serves as the mechanism through which certain antioxidant molecules can effectively inhibit the inflammatory process (11). The significant impact of ROS and inflammation extends across a wide range of unrelated diseases, including nervous system disorders, gastrointestinal autoimmune conditions and even FM. There is substantial evidence indicating a connection between mitochondrial dysfunction and elevated inflammation levels in FM (9, 11), with patients exhibiting higher plasma levels of interleukin-6 (IL-6) and interleukin-8 (IL-8) compared to healthy individuals (12). In fact, there is evidence suggesting that the levels of circulating cytokines in FM patients play a role in its pathophysiology (13).

Recently, several authors have undertaken studies to identify biomarkers linked to FM by analyzing plasma proteomic profiles using advanced proteomic techniques. Ramírez-Tejero et al. (14) identified 33 proteins exhibiting differential expression in FM patients compared to controls, with a majority of proteins associated with inflammatory processes. Another study (15) revealed differences in proteins involved in inflammatory, metabolic, and immune processes, demonstrating a correlation between these proteins, patients’ pain perception and psychological distress. Han et al. (16) discovered 22 differentially expressed proteins in FM patients compared to pain-free controls primarily associated with blood coagulation processes, immune response and interactions with extracellular matrix receptors. Collectively, these findings highlight the role of coagulation, inflammation and immune response in the pathogenesis of the disease.

The direct relationship of mitochondrial functioning with energy consumption in certain human tissues makes the musculoskeletal and nervous systems more dependent on ATP metabolism and, consequently, on mitochondrial homeostasis. Insofar as muscles, the degenerative alterations observed in muscle membranes, mitochondria and capillary vessels in FM could potentially be linked to deficiencies in membrane ion channeling, oxygen and metabolite transport, as well as ATP production through oxidative phosphorylation (17). In the context of the nervous system, recent studies have described FM as a disorder involving pain regulation and central sensitization (1), as well as a nociplastic disease (18), as pain management is among the most affected factors of the pathology, whose patients usually suffer from hyperalgesia and allodynia. The enhancement of secondary hyperalgesia is proposed to be driven by the activation of N-methyl-D-aspartate (NMDA) receptors in the spinal cord’s dorsal horn and periaqueductal gray region, leading to central sensitization. Neurons containing NMDA receptors become hypersensitive to stimulation when their ATP levels decrease, resulting in increased NMDA activity, temporal summation of pain and long-term potentiation and causing prolonged synaptic activity (12). In fact, it has been proved that individuals with FM exhibit alterations in pain regulation, such as increased neuronal activity in regions associated with pain processing (1), higher levels of excitatory neurotransmitters such as glutamate and lower levels of inhibitory neurotransmitters such as serotonin and norepinephrine (18). Furthermore, control of behavior and cognitive functioning is among the primary functions of the central nervous system (CNS). Studies have shown that alterations in the levels of antioxidant enzymes are linked to the underlying mechanisms of specific psychiatric disorders, including depression and anxiety, which are two of the most prevalent symptoms in FM (17).

It is widely recognized that the CNS plays a part in the development of FM, although the precise mechanism behind this connection is still under investigation. However, the gut-brain axis has become an interesting field to explore. Gut microbiome refers to the complete collection of bacteria, archaea, fungi, viruses, protozoa and helminths that exist in the gastrointestinal tract, as well as their genome and different metabolites. Throughout adulthood, the gut microbiota of a healthy individual is primarily dominated by four main phyla: *Bacteroidia*, *Firmicutes*, *Actinobacteria* and *Verrucomicrobia*. However, as individuals progress into old age, the microbial composition of the gut undergoes notable changes. Specifically, there is an increased proportion of *Bacteroides* spp. observed, along with distinct abundance patterns of *Clostridium* groups that differ between elderly individuals and younger adults (19). Its composition is dynamic and is influenced by both the host and the surrounding environment (20). A significant breakthrough has been made in understanding how the microorganisms residing in our gut can actively regulate brain function and behavior. This remarkable connection implies various components like the CNS, the enteric nervous system (ENS) and the sympathetic and parasympathetic branches of the autonomic nervous system, as well as neuroendocrine and neuroimmune pathways (21). This bidirectional communication between the gut and the brain enables the CNS to exert its influence over critical functions of the gastrointestinal (GI) tract. Remarkably, it also allows signals originating from the GI tract to have an impact on CNS function in return (19). The gut-brain axis plays a vital role in maintaining homeostasis and regulating a wide range of physiological functions. It encompasses motor, sensory, autonomic and secretory functions of the GI tract, influencing processes from energy metabolism to mood regulation. This axis relies on an intricate network of communication and involves extensive neuronal connections with afferent fibers projecting from peripheral tissues to higher-order processing centers in cortical CNS structures, as well as efferent projections from the CNS to the smooth muscle in the intestinal wall (22). The signaling within this axis operates through various interconnected mechanisms which include the activation of afferent sensory neurons of the vagus nerve, neuro-immune pathways and neuroendocrine pathways, as well as the involvement of microbial metabolites such as short-chain fatty acids (SCFAs) and microbial-derived neurotransmitters (21). Remarkably, some bacteria exhibit receptors for certain neurotransmitters and can even produce substances that allow them to communicate at the CNS level. Through their interaction with the primary role of the vagus nerve, these bacteria can modulate the activity of the hypothalamic-pituitary-adrenal (HPA) axis, showcasing the profound impact of the gut-brain axis on health homeostasis (23). Some bacterial neurotransmitters are noradrenaline, acetylcholine, GABA and serotonin. While serotonin is predominantly recognized for its role as a neurotransmitter in the brain, an astonishing 95% of serotonin in the body is actually found within the gut (22). This neurotransmitter plays crucial roles in regulating mood, cognitive functioning and central processing of sensory signals involved in pain processes (24). Stress is believed to be a contributing factor to alterations in the integrity of the epithelial barrier in the gut. This compromised barrier can lead to increased intestinal permeability, allowing gram-negative bacteria to translocate across the mucosal lining. Consequently, this situation enables direct interactions between humoral and cellular mediators with immune cells and the ENS, triggering an immune response characterized by heightened production of inflammatory mediators (22). As a result, various studies have observed changes in intestinal microbiota composition in several disorders, including gastrointestinal, rheumatic and metabolic conditions (20). Strikingly, Clos-García et al. (25) discovered a decrease in some bacterial strains in FM patients, specifically those associated with a healthy microbiome. These strains are involved in the production of SCFA and the depletion of *Firmicutes* phylum abundance. Additionally, the study revealed that the most affected metabolic pathways were connected to neurotransmitters such as glutamate and nitric oxide, highlighting once again the central role of the CNS in this syndrome.

The dietary habits of individuals play a key role in influencing the gut microbial community and its metabolic activities. Among healthy dietary choices, Mediterranean-style diets stand out, as they are associated with the prevention of various diseases, including cardiovascular and metabolic disorders, colorectal cancers and other chronic and acute processes (26). The positive effects of such diets are likely due to their high content of fibers, mono-and polyunsaturated fatty acids, antioxidants and polyphenols (26). Research has shown that adopting a Mediterranean-style diet leads to improvements in serum inflammation biomarkers and gene expression profiles (nutrigenomics) (27). Olive oil is an essential element in the Mediterranean diet and is known for its beneficial properties. Olive oil polyphenols possess a range of health benefits, including antioxidant, anti-inflammatory, antimicrobial, antiviral, anti-atherogenic, anti-thrombotic, anti-mutagenic and hypoglycemic characteristics. With regard to oxidative stress, consumption of high-phenol olive oil can help reduce cellular oxidative damage. Furthermore, it has the potential to lower the concentration of inflammatory markers and to enhance antioxidant capacity (28). Testing of this nutritional intervention as a therapeutic treatment in FM patients has shown that beneficial results are obtained in relation to oxidative DNA damage and antioxidant levels (29). These results could be explained by the close relationship between nutrient absorption and an adequate mitochondrial function.

In summary, FM is a chronic and complex condition that is highly underdiagnosed due to the lack of reliable biomarkers that might facilitate accurate diagnosis and disease monitoring. Hence, the primary focus of this study is to develop a targeted panel of specific plasma and fecal biomarkers capable of diagnosing this condition from readily obtained biological samples. Furthermore, the secondary objective is to investigate how nutrition can influence the modulation of these biomarkers. Identification of accurate biomarkers through this study is the key to advancing our understanding and management of FM, ultimately leading to improved patient outcomes.

## Materials and methods

2

### Study design

2.1

This is a randomized, prospective, low-interventional, double-blinded and placebo-controlled clinical trial. This study will be performed on adult women who meet ACR diagnostic criteria for FM (FM group), along with age-matched healthy volunteers (CONTROL group). The double-blinded, placebo-controlled, randomized experiment will be conducted by using extra virgin olive oil (EVOO) as treatment and olive oil (OO) as placebo, being under nutritional intervention in adherence to a Mediterranean diet supplemented with one of the olive oils for 6 months since the first sample collection. The participants will be assigned to each group randomly, using the balanced block randomization method. Briefly, once participants have been chosen for project enrollment, they will be tagged with an ordinal numeric code with three numbers by an employee from the company not related with the project nor the laboratory. This same employee will decide the codification of treatment (EVOO) and placebo (OO) groups, by assigning them an “A” or a “B” letter. Then, a second employee neither related with project or lab workflow, will randomly allocate these codes to 8-individuals blocks composed by 4 patients and 4 healthy volunteers. These blocks will be assigned to a treatment group by following the pattern ABBAABBA. In this process, this second employee will only have access to the date and time in which the participation form was completed as a unique identifier, as well as the condition of the participant: patient (FM) or healthy volunteer (CONTROL). This process will ensure that no one can link any code to its health condition, neither to participants’ data. Both processes will be reflected in patients’ database and documented in a password encrypted word file that will be also kept physically in a key-protected drawer during the entire project. The blinding method will be maintained until the data have been fully analyzed, and once this information is required to write the scientific communications that will be generated. As a result, both, patients and researchers will be fully blinded about treatment to be taken and health conditions from each participant code. Furthermore, by following the balanced block randomization method, the treatment and placebo group will comprise the same number of patients and healthy individuals. The study will span a total duration of 12 months, during which four blood and stool samples will be collected from each participant: the first before nutritional intervention (T_0_), the second after 3 months of nutritional intervention (T_1_), the third at the conclusion of the six-month nutritional intervention (T_2_) and the fourth 6 months after the end of the intervention (T_F_). This final timepoint have been included to check whether the identified biomarkers that response to nutritional intervention would change back again to the baseline, indicating a strong dependance between nutritional habits and these specific biomarkers. Figure 1 illustrates the workflow that will be followed in this study.

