### Intervention

2.3

In order to test this new tool as a patient monitoring instrument, the study will investigate the responsiveness of the new panel of markers associated with FM in the assessment and monitoring of treatment. The treatment group will undergo a nutritional intervention based on the Mediterranean diet using EVOO as a supplement, and the placebo group will receive OO. Both groups will be under nutritional control, with regular follow-up calls (twice a month) by their assigned nutritionist. Dietary adherence will be monitored by 24 h dietary recall, as well as a deeper nutritional interview. To avoid excessive withdraw, nutritionist will provided a wide repertoire of foods and cooking tips. The participants will receive a semi-customized list of three-week menus to exchange throughout the intervention (Supplementary material S2). Additionally, they will consume 50 ml of the assigned raw oil, freely distributed through the main meals during the day. This treatment regimen will be administered over a period of 6 months. Figure 2 illustrates the design of the nutritional intervention that will be followed.

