#### Plasma proteome analysis

2.4.2

Whole blood samples from participants will be collected through venipuncture performed by a healthcare professional. The samples will be collected in two tubes containing heparin-lithium as an anticoagulant. Moreover, to minimize circadian fluctuations of the markers, the blood samples will be taken at the same time of day and participants will have fasted beforehand. While one of the tubes will be used for oxidative stress and mitochondrial metabolism analysis, the other one will be transferred to a 15 ml Falcon tube and then centrifuged at 2,300 RCF for 10 min at 4°C. This process will isolate the plasma, the sample to be used in the proteome analysis that will be aliquoted and stored at −80°C until batch analysis (maximum storing: 5 months). To analyze the plasma proteome, liquid nano-chromatography coupled to the tandem mass spectrometry (nLC-MS/MS) proteomic method will be applied. This analysis will utilize the EvoSEP chromatograph,^1^ which is one of the highest resolution and processing chromatographs available. It is a unique instrument in Spain and is accessible through the services of the BioGUNE Cooperative Research Center in Biosciences located in Biscay, Spain. The processed data will be analyzed with the search engines MASCOT (MatrixScience) and/or PEAKS (Bioinformatics Solutions Inc). Label-free quantification differential proteomics will be performed using PEAKS (Bioinformatics Solutions Inc) and/or MaxQuant software. Quality control of samples will be applied at each step through protein-suitable techniques such as Bradford quantification, electrophoresis and/or Ponceau staining.

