#### Oxidative stress analysis

2.4.3

Oxidative stress levels will be evaluated at the beginning (T_0_) and end (T_F_) of the nutritional intervention by measuring the TAC in whole blood. This will be done using the eBQC device (Bioquochem, Asturias, Spain).^2^ A 100 μL heparin-lithium anticoagulated blood sample will be applied to a test strip, which will then be used to evaluate the global antioxidant status by measuring Q1, Q2 and QT twice. Q1 represents the antioxidant capacity of compounds exhibiting the highest rate of free radical scavenging. These antioxidants are characterized by their rapid action and are the first to undergo oxidation. Notable examples of these fast-acting antioxidants include uric acid, ascorbic acid (vitamin C), GSH, vitamin E, CoQ10 and carotenoids (32, 33). Q2 refers to the antioxidant capacity of compounds that scavenge free radicals at a slower rate. These are known as slow-acting antioxidants. Some examples are polyphenols, alpha-lipoic acid, resveratrol and astaxanthin (32, 33). To quantify the overall antioxidant capacity, the device calculates QT, which results from the combination of contributions from both Q1 and Q2. The eBQC device utilizes electrochemistry to obtain the results. By applying variable voltage, the sample is oxidized to activate the antioxidants. As a result of this activation, electrons are released and then detected to determine the antioxidant capacity (33).

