#### Mitochondrial metabolism analysis

2.4.4

PBMC will be isolated by a protocol based on ammonium chloride from whole heparin-lithium anticoagulated blood. The samples will be mixed with this solution and then exposed to agitation and centrifugation at 600 RCF for 10 min at 4°C. The resulting cell pellet will be stored at −80°C. Protein extracts will be obtained from PBMC using a protein extraction buffer in white blood cells, containing sucrose 0.32 M, Tris-HCl 0.01 M, magnesium chloride 0.005 M, 1% of Triton-X and protease inhibitors. The separation of these extracts will be carried out using acrylamide gel electrophoresis (SDS-PAGE). The western-blot technique will be used to analyze the abundance of two proteins associated with mitochondrial metabolism: VDAC, a cation channel located in mitochondrial mass in directly linked to mitochondrial mass, and MAP1LC3B (Figure 3), an autophagosome-related protein used to assess autophagy. Additionally, vinculin will be used as a loading control throughout this procedure. To determine mitochondrial ratio, normalized levels of VDAC and MAP1LC3B will be indexed in a numerical algorithm designed with this purpose.

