#### Microbiota and intestinal permeability analysis

2.4.5

Participants will collect fecal samples using the DANASTOOL sample collection kit (Danagen; Barcelona, Spain). They will use a Fe-Col^®^ Faecal sample collection paper (Alpha Laboratories; Hampshire, United Kingdom) as a stool-catch platform. The participants will scoop a small portion of stool into the provided stool tube, which contains a liquid DNA/RNA stabilization solution. Following collection, all samples will be stored in accordance with established quality standards. Since the DANASTOOL sample collection kit has a DNA/RNA stabilization solution, samples were stored at room temperature until batch analysis. DNA extraction from fecal samples will be carried out using the DANAGENE MICROBIOME FECAL DNA KIT (Danagen; Barcelona, Spain). Briefly, 1 ml of homogenized sample was transferred to a tube containing beads to ease sample disruption. Then, samples were incubated at 70°C during 10 min. After incubation step, a thorough vortexing and centrifugation steps were applied. The upper phase was then transferred to a filtering column to extract DNA by centrifugation. The extracted DNA will then be used to analyze the composition of the gut microbiota. This analysis will involve amplicon metagenomics sequencing, in which amplicons of V3–V4 regions from the 16S rDNA will be sequenced using the Illumina MiSeq platform at HelixBioS (Madrid, Spain) facilities. A tagging and barcoding process suitable for Illumina technology will be conducted, according to manufacturer instruction. Each sample will undergo individual quantification, pooling, washing and titration using qPCR. The sequencing will be performed on the MiSeq platform with a fragment size ranging from 2 × 250 to 2 × 300, with the aim of generating 150,000 to 200,000 reads per sample. We will set the minimal number of reads per sample at 50,000 as quantity threshold, and Phred Score at Q30 as quality threshold. Samples with an average trimmed read length below 280 bp will be discarded. All these quality control procedures will be applied through MultiQC software (36) and sequencing results will be analyzed with USEARCH V11.1. Briefly, the reads will be cleaned using the UCHIME algorithm to eliminate “singletons” sequences (those that only had one copy in the total sequences), chimera sequences and possible artifacts. ZOTUs clustering will be carried out using the UNOISE algorithm at 99% identity (similarity). The sequences will be then aligned against the taxonomic database developed for the study of the intestinal microbiota, HUMAN GUT 16S (HelixBioS), with an alignment cut-off point of 99% (identity) using the algorithm USE-LOCAL. The results will be finally processed with phyloseq (37) and DESeq2 (38).

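### A responder's return to baseline at T_F does not by itself show dependence on nutritional habits: chance responders fall back through selection, and only the oil is randomised

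*Protocol article*

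**What the plan says.** Section 2.1 (Study design) sets four visits. T0 precedes the intervention and T1 is at three months. Next comes "the third at the conclusion of the six-month nutritional intervention (T_2"). The last is "the fourth 6 months after the end of the intervention (T_F"). The reason given for this last visit is a question: "whether the identified biomarkers that response to nutritional intervention would change back again to the baseline, indicating a strong dependance between nutritional habits", meaning that such markers depend on diet. The sentence starts from markers already identified as responders and does not say against what the return is judged.

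Section 2.3 (Intervention) puts both arms on the Mediterranean diet, with EVOO in one and OO in the other: "Both groups will be under nutritional control, with regular follow-up calls (twice a month) by their assigned nutritionist". Section 2.2.2 (Inclusion criteria) also requires a diet on Mediterranean principles at entry.

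Section 2.4.6 (Statistical analysis) plans a pre-post ANCOVA of treatment against placebo, with multiple comparison correction. It does not mention T_F.

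Storage differs by sample. Plasma for the proteome is kept "until batch analysis (maximum storing: 5 months"). For stool, "samples were stored at room temperature until batch analysis", and for blood cells, "The resulting cell pellet will be stored at −80°C"; neither has a stated limit.

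**The concern.** The stated reading is conditional on a marker having responded. A marker can be called a responder because the intervention moved it or because noise did. In the second case its next measurement is expected to lie closer to baseline, which is the pattern the article would count as evidence. The check therefore tends to endorse the false responders it should expose.

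The conclusion is also drawn about nutritional habits in general, while the randomised difference between the arms is the oil. For plasma proteins, a third explanation of a within-person return, assay drift between batches, is built in by the storage limit.

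At stake is the only stated purpose of T_F, and with it part of the secondary objective: how nutrition modulates the markers. The primary aim, a diagnostic panel, does not rest on this reading.

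**Working it through.** **Inputs.** From the documents: visits at 0, 3, 6 and 12 months (2.1); plasma cap 5 months (2.4.2); 250 participants (2.2.2); α = 0.05 (2.4.6). Assumed: 125 per oil (250/2, from balanced allocation), two-sided tests, unit variance at each visit, and equal correlation ρ between any two visits. The documents give no ρ, so a range is shown. That T2 is the visit at which responders are identified is an inference; section 2.1 names none.

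The plan gives no figure for this reading. Its one computed figure, the minimum of 206, plays no part here. It reproduces closely: with P = 0.0755, 1.96² × P(1−P)/(P/2)² = 188.2, and 188.2 × 1.10 = 207.0.

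**Step 1: expected fall-back of a null marker, EVOO-OO contrast adjusted for T0.** The share of the T2 effect expected at T_F is the partial correlation of T2 and T_F given T0:

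(ρ − ρ²)/(1 − ρ²) = ρ/(1 + ρ)

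- ρ = 0.3: 0.3/1.3 = 0.23
- ρ = 0.5: 0.5/1.5 = 0.33
- ρ = 0.7: 0.7/1.7 = 0.41
- ρ = 0.9: 0.9/1.9 = 0.47

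This share does not depend on the selection threshold. A stricter threshold lets fewer null markers through, but those that pass shrink by the same proportion.

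**Step 2: simulation.** Null markers (20,000 per setting, 125 per oil) were selected by ANCOVA at T2 with p < 0.05 and then read at T_F.

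| ρ | effect retained at T_F | no longer significant at T_F |
|---|---|---|
| 0.3 | 24% | 91% |
| 0.5 | 34% | 88% |
| 0.7 | 41% | 86% |
| 0.9 | 47% | 83% |

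With 62 per oil (about 250/4, the FM patients alone) and ρ = 0.5, the figures are 35% and 89%.

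**Step 3: the same for a within-person reading.** For a null marker, Cov(T2−T0, T_F−T0) = 1−ρ and Var(T2−T0) = 2(1−ρ), so half of the change is expected to remain whatever ρ is. The simulation gave 49-51%, with 80-83% no longer significant.

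**Step 4: storage against visit spacing, plasma only.**

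| pair | gap (months) | one batch possible within 5 months? |
|---|---|---|
| T0-T1 | 3 | yes |
| T1-T2 | 3 | yes |
| T0-T2 | 6 | no |
| T2-T_F | 6 | no |
| T1-T_F | 9 | no |
| T0-T_F | 12 | no |

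The three samples that a response-and-return reading compares in one participant therefore fall in three different batches.

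**Step 5: what a batch shift does to the randomised contrast.** A shift common to both arms cancels in EVOO minus OO. With shifts of 0.1, 0.2 and 0.3 SD at T2 (assumed; ρ = 0.5), ANCOVA selected 4.8%, 5.2% and 4.9% of null markers, against a nominal 5%. If the arms are unequally spread over batches, the bias is the shift multiplied by the difference between arms in the share of samples run in the shifted batch. It is zero only when that difference is zero.

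**The case against.** The strongest reply is that the comparator exists. There is a concurrent randomised OO arm, and section 2.4.6 already plans a multiplicity-corrected ANCOVA of treatment against placebo. A reader might infer from section 2.1 that reversal has no comparator at all. The documents do not support that: the sentence leaves the contrast open, and for the oil a valid one is at hand. What remains is that the article never connects that ANCOVA with the T_F question, that the correction does not remove shrinkage, and that the OO arm cannot support a claim about diet in general.

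A reader might also infer that visit and batch are completely confounded. That holds only within a participant. With staggered enrolment, one batch can hold different visits from different women, and T1 plasma can share a batch with T0 or T2. Nor does the argument extend to stool or blood cells, which have no stated cap. Total antioxidant capacity is a separate case: section 2.4.3 says "Oxidative stress levels will be evaluated at the beginning (T_0_) and end (T_F_) of the nutritional intervention", so it has no T2 value, and its label for T_F conflicts with section 2.1.

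It is tempting to conclude that batch drift would make most unaffected proteins look responsive. That would need a within-arm test of change, which the article does not plan, and a shift whose size it does not give. The planned contrast keeps its error rate under a common shift.

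The article says only that a return would indicate dependence; it does not claim proof, and this is one sentence of rationale for a follow-up visit. Batch procedures are commonly left to laboratory documents, so their absence is no fault. The storage limit and visit spacing are stated, however, and so is the inference they affect.

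Finally, the simulated percentages apply to markers that are truly null. They do not tell what share of declared responders would be false, and loss of significance is only a stand-in for return to baseline, which the article does not define.

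**Conclusion.** The point holds as a limit on what T_F can show. Return to baseline among identified responders is not sufficient evidence of dependence on nutritional habits. Under equal visit correlation of 0.3 to 0.7, roughly 20-40% of a null marker's apparent EVOO-OO effect remains at T_F; at 0.9 it is still under half. The exact share rests on the assumed correlation and on selection at T2, but the direction does not change over the range examined.

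Any conclusion protected by randomisation concerns EVOO against OO. For plasma proteins, a within-person return may additionally be batch drift; the randomised contrast is safe from a common shift only if the arms are balanced within batches. That balance is not automatic: read literally, section 2.1 assigns blocks of eight to an oil, so running samples in block order could align batch with arm.

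**What to change.** 1. Extend the section 2.4.6 ANCOVA to the T_F question. Estimate the T0-adjusted EVOO-OO difference at T2 and at T_F for all markers tested, not only responders, and give a confidence interval for the change in that difference. Tested without prior selection, a null marker shows reversal only at the chosen error rate.
2. Reword section 2.1 so that the conclusion is limited to the oil, and drop the claim of strong dependence for a within-person return.
3. For the plasma proteome, balance both oils and FM/CONTROL in each batch, include one pooled plasma reference sample in every batch, and put batch in the model. The 5-month cap can then stay.

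The cost is a change of wording, a run-order list that keeps the blinding (for instance from the independent employee who holds the codes), and a few reference injections per batch. The price in content is a more modest conclusion about T_F.
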